Topical administration options have fewer systemic side effects. Preemptive injection of local anesthetics can significantly reduce postoperative pain, although the analgesic effect is maintained for a relatively short period of time. Incidences of technical failure or local anesthetic toxicity from wound catheters were found to be low in a study by Liu et al. [9], although other reports have raised concerns about probable wound infection from the existence of a catheter [10]. Furthermore, indwelling catheters come with a risk of complications such as prolapse or obstruction of the catheter. Cost-effectiveness, optimal site for catheter placement, and optimal dosage are also factors to be considered [9]. Techniques such as epidural analgesia and nerve blockade may have a possible high failure rate and not be cost effective, but they can deliver better postoperative analgesia [11–13]. Gurbet et al. [1] reported that preemptive infiltration of bupivacaine or levobupivacaine combined with methylprednisolone, a short-acting glucocorticoid, can effectively control pain after unilateral lumbar laminectomy. However, this solution has a shorter duration of action, and the study involved merely 24-h postoperative observation and only 60 participants. Ersayli et al. [14] reported that, compared to infiltration at wound closure, preemptive injection of bupivacaine or bupivacaine-methylprednisolone into muscles near the incisional site provided more effective analgesia after lumbar discectomy, and they concluded that methylprednisolone combined with local anesthetic was not superior to the analgesic effect of local anesthetic alone. However, in the study [14], 75 participants were enrolled with only 15 in each group. Therefore, it is necessary to observe more cases to explore other compatibilities of drugs with longer duration of action and stronger analgesic effect.

Betamethasone, a stereoisomer of dexamethasone, is a long-acting corticosteroid which has longer lasting anti-inflammatory properties because of its partial presence in particulate form in ropivacaine, acting as a local reserve [15]. Whether betamethasone combined with local anesthetic for laminoplasty or laminectomy has better analgesic effects than the local anesthetic alone has not been reported yet. Therefore, a detailed study is needed to compare the postoperative analgesic efficacy of preemptive infiltration of betamethasone plus ropivacaine and ropivacaine alone for laminoplasty or laminectomy.

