### Postoperative recording parameters for up to 48 h

The parameters will be recorded at 2, 4, 8, 24, and 48 h after surgery by a research member, who will visit each patient in person. Pain scores will be measured using the VAS score: an 11-point VAS score during movement (VAS_M_) and at rest (VAS_R_) will be recorded, with 0 indicating no pain and 10 indicating the most severe pain imaginable.

Time of first analgesic demand will be indicated by the first press of the analgesic demand button on the PCA device. The time of first analgesic demand, total press count, the cumulative butorphanol dose for four separate periods (0–4, 4–8, 8–24, and 24–48 h), and total butorphanol dose at 48 h will be recorded.

The Patient Satisfaction Score (PSS) used in this study will comprise points 1–4, based on the study by Mobbs et al. [17].

Postoperative nausea and vomiting (PONV) and Ramsay Sedation Scale (RSS) scores will also be recorded. PONV will be measured using an ordinal scale with the following values: 0 no nausea, 1 mild nausea not requiring treatment, 2 nausea requiring treatment, 3 vomiting. The RSS uses a 6-point scale to assess sedation levels, with 1 indicating agitated, anxious; 2 cooperative; 3 only responds to commands; 4 strong response to glabellar tapping or noisy stimulants; 5 weak response to glabellar tapping or noisy stimulants; 6 no response.

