### Primary outcome

The primary outcome will be the cumulative butorphanol dose during the 48 h after surgery via the PCA device.

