### Sample size {14}

Ersayli et al. reported that total morphine consumption at 24 h was 13.2 ± 4.1 mg after lumbar discectomy for patients who received local wound infiltration of bupivacaine alone just before incision [14]. The analgesic effect of 1 mg morphine is the same as that of 3.75–7 mg butorphanol. This dose of morphine could be converted into an equianalgesic dose of butorphanol (with conversion factor 1 mg morphine = 3.75–7 mg butorphanol). Therefore, we have estimated that total butorphanol consumption will be about 120.0 ± 90.0 mg at 48 h after laminoplasty or laminectomy for the patients who received preemptive analgesia with local anesthetics.

Nakai et al. suggested that local wound infiltration by addition of betamethasone could reduce the dose of analgesics by about 45% in the 24 h after lumbar discectomy [18]. Therefore, we hypothesize that the cumulative butorphanol consumption during the 48 h after lumbar discectomy will be 120.0 ± 90.0 mg in the control group and 70.0 ± 50.0 mg in the treatment group. Based on a 90% power with a two-sided α of 0.05 and a dropout rate of 20%, we have calculated that at least 116 patients (58 per group) will be required.

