### Statistical methods

#### Statistical methods for primary and secondary outcomes {20a}

Statistical analyses will be performed using the statistical package SPSS software 25.0. A Kolmogorov-Smirnov test will be used to assess normality of variables. Data for normal distribution will be presented as mean ± SEM (standard error of the mean). Variables for skewed distributions will be described as median and interquartile range (IQR). Categorical variables will be expressed as frequencies with percentages.

Comparisons between the groups will be carried out using an independent *t* test to compare normally distributed data, the Mann-Whitney *U* test for skewed data, and a χ^2^ test or Fisher’s exact test to compare categorical data such as safety analyses with the incidence of AEs. For numerical data collected at different time points throughout the course of 6 months (e.g., PCA cumulative consumption of butorphanol, PONV, RSS, PSS, and ODI), repeated measures analysis of variance will be performed between the two groups. The significance level will be set at *P* < 0.05.

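### Butorphanol dose over windows of 4, 4, 16 and 24 h goes into a repeated-measures ANOVA with no common time base, so its time and group-by-time terms cannot be read as onset or duration of opioid sparing

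*Protocol article*

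**What the plan says.** Under *Postoperative recording parameters for up to 48 h*, the protocol article states that "the cumulative butorphanol dose for four separate periods (0–4, 4–8, 8–24, and 24–48 h), and total butorphanol dose at 48 h will be recorded". *Secondary outcomes* lists the four window doses again. Table 1 marks cumulative butorphanol consumption at 4 h, 8 h, 1 day and 2 days.

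*Statistical methods for primary and secondary outcomes {20a}* covers numerical data collected at several time points and gives as examples "PCA cumulative consumption of butorphanol, PONV, RSS, PSS, and ODI), repeated measures analysis of variance will be performed between the two groups". It does not say whether the butorphanol values are window doses or running totals. It mentions no rate, offset or other adjustment for window length. It names no time or group-by-time hypothesis.

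The primary outcome is separate: "The primary outcome will be the cumulative butorphanol dose during the 48 h after surgery via the PCA device". The same section also provides simple two-group tests: "Comparisons between the groups will be carried out using an independent *t* test to compare normally distributed data, the Mann-Whitney *U* test for skewed data".

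**The concern.** The four windows last 4, 4, 16 and 24 h. A patient who uses butorphanol at a steady rate therefore records six times as many mg in the last window as in the first, and a steady treatment difference in mg/h grows sixfold in the same way. A repeated-measures ANOVA on these values tests whether mean dose changes across windows and whether the arm difference changes across windows. Both can come out significant although nothing changes per hour.

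This matters because *Background and rationale {6a}* justifies the trial by the need to "explore other compatibilities of drugs with longer duration of action and stronger analgesic effect". The window doses show when within 48 h opioid use differs between arms, so a group-by-time result on them could easily be taken as evidence on duration. A steady effect could look like a growing one, and an effect limited to the early hours could be hidden by the two long windows.

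**Working it through.** **Inputs.** Windows: *Postoperative recording parameters* and *Secondary outcomes*. Means and SDs at 48 h: *Sample size {14}*, "120.0 ± 90.0 mg in the control group and 70.0 ± 50.0 mg in the treatment group". Power 90%, two-sided α 0.05 and dropout 20%: same section.

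**1. The plan's own figure.** Common SD = √((90² + 50²)/2) = 72.8 mg; difference = 120 − 70 = 50 mg. A two-sample t test with 46 per group has power 0.903. Allowing for dropout, 46/0.8 = 57.5, so 58 per group and 116 in total. The stated size is reproduced. It rests on the 48-h total alone and uses no window data.

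**2. Window arithmetic under a constant hourly rate.** Control: 120/48 = 2.50 mg/h. Treatment: 70/48 = 1.46 mg/h. Difference: 50/48 = 1.04 mg/h throughout.

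| Window | Hours | Control, mg | Treatment, mg | Difference, mg | Difference in running total, mg |
|---|---|---|---|---|---|
| 0–4 h | 4 | 10 | 5.8 | 4.2 | 4.2 |
| 4–8 h | 4 | 10 | 5.8 | 4.2 | 8.3 |
| 8–24 h | 16 | 40 | 23.3 | 16.7 | 25 |
| 24–48 h | 24 | 60 | 35 | 25 | 50 |

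**3. Group main effect.** On window doses, each patient's mean over the four windows is the 48-h total divided by 4. The group test is therefore the t test of the total, and window length does not touch it. On running totals, the first window is counted four times, the second three times, the third twice and the fourth once. Under a constant rate the weights are 4×4, 3×4, 2×16 and 1×24 = 16, 12, 32 and 24 out of 84, or 19/14/38/29%. The shares in the 48-h total are 8/8/33/50%. Early doses are over-weighted.

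**4. Simulation of the group-by-time test** (2,000 trials per setting, Greenhouse-Geisser correction, P < 0.05). Assumptions not in the protocol: gamma-distributed patient effects, scaled so that the CV of the total is 90/120 = 0.75 in control and 50/70 = 0.71 in treatment, and a within-patient window CV of 0.2, 0.4 or 0.6. The last four rows use 58 per group and window CV 0.4.

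| True situation | mg per window | Running totals | mg/h |
|---|---|---|---|
| Constant effect in mg/h, 58 per group | 80–97% | 97–98% | 4–5% |
| Constant effect in mg/h, 46 per group | 70–92% | 92–94% | 3–4% |
| Constant rate, no effect (46 or 58) | 4–6% | 4–6% | 4–5% |
| 80% lower use in 0–8 h only | 20% | 7% | 100% |
| Halved use in 8–48 h only | 100% | 99.8% | 99.8% |
| Use at 0.42 of control in 24–48 h only | 100% | 90.5% | 99.8% |
| Falling use, constant ratio 70/120 | 80% | 97% | 76% |

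The falling-use row takes control rates of about 5.0, 4.0, 2.75 and 1.67 mg/h, which again sum to 120 mg over 48 h. With constant hourly rates, the time effect was significant in 100% of trials on mg per window and on running totals, and in 3–5% on mg/h.

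**The case against.** The strongest case on the other side has five parts.

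- *No scaling is inferred from silence.* The article condenses a fuller plan, and an analysis plan not shown here could add a rate. That stands as a limit: one cannot say that the trial will model raw mg. But the article does fix the outcome (dose over unequal windows) and the model, and wherever it defines the outcome it is a dose, never a rate. Window doses and running totals are both plausible readings, and both carry the problem.
- *The interaction is not an artefact of window length.* A reader might infer that a significant group-by-time term would reflect window length and not drug action. That is too strong. With no group difference the test kept to about 5%, and real late effects drove it to significance in nearly every trial. The term is mixed.
- *No section says the interaction will be read as duration.* Correct. That the authors would report a steady effect as a growing one is a prediction, not something the protocol states.
- *Other data bear on timing.* Time of first analgesic demand and serial VAS are secondary outcomes. A t or Mann-Whitney test within a single window gives the same P value in mg and in mg/h. This stands: the fault lies only in the time and group-by-time terms and, for running totals, in the weighting of the group effect.
- *mg/h is not a complete cure.* This stands. If use falls over time and the effect is proportional, an interaction can remain on mg/h (76% in the one profile tried). *Sample size {14}* itself cites a proportional reduction of about 45%.

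**Conclusion.** The point holds as a minor one on a secondary outcome. On mg per window or on running totals, the time and group-by-time terms for butorphanol are confounded with window length and should not be read as onset or duration of opioid sparing.

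The sixfold rise in the arm difference (4.2 to 25 mg) is arithmetic and needs only a constant hourly rate. The rejection rates of about 70–97% on mg per window, and the 20% detection of an effect confined to 0–8 h, depend on assumed patient and window variation. The size of these figures is therefore indicative. Under a constant hourly effect the direction was the same at every window CV and sample size tried. Multiplying all doses by one constant would change the mg figures but no P value.

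A reader might also infer that the main efficacy result is at risk. It is not: the 48-h total, its two-group test and the sample size of 116 do not depend on the windows.

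**What to change.** In *Statistical methods for primary and secondary outcomes {20a}*, state that:

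1. window doses are divided by window length (mg/h over 0–4, 4–8, 8–24 and 24–48 h) before the repeated-measures analysis;
2. running totals are not used as the repeated measure;
3. the arm difference in mg/h is reported for each window, with the arm ratio per window as a supplement, so that a proportional effect on falling use is not mistaken for a changing one.

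Keep the 48-h total in mg as the primary outcome.

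The cost is a sentence or two. No new data are needed, because the pump system described under *Additional interventions* logs drug dosage and the time of each press. The downside is that the short early windows are noisier on the mg/h scale.

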#### Methods in analysis to handle protocol non-adherence and any statistical methods to handle missing data {20c}

All researchers will be trained referring to the same training protocol. Protocol modifications will not be expected. Missing intraoperative data, if any, will be obtained from the electronic hospital files. Postoperative evaluation at specified time points is mandatory, and missing postoperative data are not to be anticipated. Analyses of all outcomes will be performed according to the intention-to-treat principle, and once enrolled, all participants will be analyzed, regardless of the findings.

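### Repeated-measures ANOVA for the 6-month secondary outcomes cannot analyse all participants once patients drop out, and it treats ordinal scores as numerical

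*Protocol article*

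**What the plan says.** All references are to the protocol article.

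- **Method.** Section {20a} introduces the longitudinal analysis with "For numerical data collected at different time points throughout the course of 6 months (e.g., PCA cumulative consumption of butorphanol, PONV, RSS, PSS, and ODI", and for these data "repeated measures analysis of variance will be performed between the two groups". The same section names SPSS 25.0 as the software.
- **Analysis population.** Section {20c} states: "Analyses of all outcomes will be performed according to the intention-to-treat principle, and once enrolled, all participants will be analyzed, regardless of the findings".
- **Missing data.** Section {20c} also says that "missing postoperative data are not to be anticipated". The only remedy it gives is retrieval of missing intraoperative data from hospital files.
- **Expected loss.** Section {14} builds in "a dropout rate of 20" per cent. Section {18b} foresees patients who do not finish the 6 months because of deviation, personal reasons or lost contact, and says that they will not be replaced.
- **Scales.** In the section on recording up to 48 h, "PONV will be measured using an ordinal scale with the following values", which run from 0 to 3. RSS has six labelled sedation states and PSS has four points.
- **Schedule.** Under Secondary outcomes, PSS and VAS are each taken at 12 times from 2 h to 6 months. ODI is taken preoperatively and at four later times. PONV and RSS stop at 48 h. WHOQOL-BREF is taken preoperatively and at 6 months.

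**The concern.** Two features of the stated method clash with other parts of the same document.

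First, classical repeated-measures ANOVA works on complete sets of values. A patient who misses the 6-month contact contributes nothing to the PSS analysis, although up to 11 of the 12 scores may be on file. The result is an analysis of completers presented as intention to treat.

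It is biased if loss is related to pain or to arm, and the document gives grounds to think it could be. The Outcomes section says that complications such as nerve-injury pain and wound infection may affect follow-up. The Discussion accepts that local steroid carries a risk of delayed healing or infection. Such losses could differ between arms.

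Second, an ANOVA on PONV, RSS and PSS compares mean category numbers. It assumes, for example, that the step from treated nausea to vomiting equals the step from none to mild. Nothing in the document supports equal spacing.

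At stake are the secondary and long-term conclusions, not the primary endpoint.

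**Working it through.** **1. The plan's own figure.** Inputs from {14}: means 120 and 70 mg, SDs 90 and 50 mg, 90% power, two-sided α 0.05, 20% dropout.

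- Root-mean-square SD = √((90² + 50²)/2) = 72.8; difference = 50.
- Normal approximation: n = 2 × (1.960 + 1.282)² × 72.8²/50² = 44.6, so 45 per group. The noncentral t calculation gives 46 (power 0.903).
- 46/(1 − 0.20) = 57.5, so 58 per group and 116 in total. The stated 116 reproduces, which confirms that the 20% is a real part of the plan's arithmetic.

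**2. Patients left for a complete-case analysis.**

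- Assumption: the planned 20% is lost by month 6. The document does not say when dropout occurs.
- Lost: 116 × 0.20 = 23.2, about 23. Left: 116 × 0.80 = 92.8, about 93.
- For PSS, five of the 12 assessments fall at 2, 4, 8, 24 and 48 h. If the 23 patients leave after 48 h, 23 × 5 = 115 of the 116 × 5 = 580 early scores are collected and then not used.

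**3. Missed single visits (illustration).** Assume that each visit is missed independently at rate p, on top of the 20% dropout. The number complete is 92.8 × (1 − p)^T.

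| p per visit | PSS, T = 12 | ODI, T = 4 postoperative |
|---|---|---|
| 1% | 82 | 89 |
| 2% | 73 | 86 |
| 5% | 50 | 76 |

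The miss rates and their independence are assumptions. Five of the 12 PSS assessments are in-person visits within 48 h, so the lower rows for PSS are probably pessimistic.

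**4. Which outcomes are affected.**

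| Outcome | Last time | Named in {20a} for this method | Affected by loss after 48 h |
|---|---|---|---|
| Butorphanol by period | 48 h | yes | no |
| PONV, RSS | 48 h | yes | no (but ordinal) |
| PSS | 6 months | yes | yes, including its early scores (and ordinal) |
| ODI | 6 months | yes | yes (no scores before 4 weeks) |
| VAS | 6 months | no; the list is of examples | only if analysed this way |
| Primary 48-h total | 48 h | single total | no |

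**5. Statements side by side.** Four statements cannot all hold: every participant is analysed; no postoperative data will be missing; 20% drop out and are not replaced; and the method needs complete data. A model that uses all observed values removes the conflict for every patient with at least one postoperative value, up to 116.

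**6. WHOQOL-BREF baseline.** With correlation ρ between the preoperative and 6-month scores, adjustment for baseline reduces the residual variance by ρ². For assumed ρ of 0.3, 0.5 and 0.7 this is 9%, 25% and 49%.

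**The case against.** The strongest reply is that this is a condensed article. A separate analysis plan may exist and may specify how missing values, covariates and covariance are handled. That holds for anything the article leaves open, and silence on those matters is not the point here. The article does not leave the method open, though: it names a method, a population and an expectation about missing data that do not fit together.

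A second reply is that the loss may be small. Section {18b} allows telephone follow-up and says that further data will be collected after withdrawal, and the early assessments are made in person. These measures reduce missingness, but the protocol still budgets for 20%. Repeated-measures ANOVA might also be loose wording for a mixed model, but nothing in the text says so.

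Third, the 48-hour outcomes, including the primary, are untouched by later loss. This stands and limits the point.

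Three stronger readings are tempting but not supported:

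- **ODI dilution.** A reader might infer that preoperative ODI enters as a fifth repeated level and dilutes the group effect, with a calculable loss of power. The protocol says neither that it enters this way nor that the group main effect is the test. A treatment-by-time test would be equally natural, so no power figure can be given.
- **Ignored baselines.** A reader might call the absence of baseline adjustment an error. An unadjusted randomised comparison is valid, only less precise, and covariates are usual content for an analysis plan.
- **Preoperative VAS.** Patients are taught the scale before surgery, but that does not oblige the trial to record a score. Asking for one would be a preference that needs new data.

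**Conclusion.** The point holds for the repeated secondary outcomes that run to 6 months, and for the ordinal scores.

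- The stated method cannot deliver the stated intention-to-treat analysis. If the protocol's own 20% are lost by month 6, about 23 of 116 patients are excluded from the PSS and ODI analyses, and from VAS if it is handled this way. This assumes the classical, complete-case form of the method. Missed single visits would exclude more, by an amount that depends on assumed rates.
- The expectation of no missing postoperative data contradicts the sample size section and {18b}, whatever method is used.
- The treatment of PONV as numerical contradicts the protocol's own description of the scale. RSS and PSS are not called ordinal in the text, but as short ordered scales they raise the same difficulty.

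The sample size stands: 46 completers per group give about 90% power for the primary total under the plan's inputs. The change should be made before the data are analysed, but it does not threaten the primary result.

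**What to change.** 1. In {20a}, replace repeated-measures ANOVA for VAS and ODI with a linear mixed model on all observed postoperative values, with treatment, time and treatment×time as fixed effects. For ODI, enter the preoperative score as a covariate and not as a repeated outcome level. The model relies on data being missing at random, and the text should say so.
2. Analyse PONV, RSS and PSS with a proportional-odds mixed model or GEE.
3. In {20c}, delete the statement that missing postoperative data are not anticipated, so that the section agrees with {14} and {18b}.
4. As an improvement rather than a correction, analyse the 6-month WHOQOL-BREF domains by ANCOVA on the baseline already scheduled.

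The cost is a change of analysis wording. No further data, visits or patients are needed, and the models are available in the software already named.
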